### **12.3 Number of Subjects**

One hundred and ninety-two (192) subjects including both sexes, aged 18 to 60 years are expected to enroll in this study. There will be 9 cohorts. The first 2 cohorts at each dose level will comprise 16 subjects while the third cohort will comprise 32 subjects, which will be enrolled in 2 successive groups of 16. The study will aim to enroll equal numbers of men and women at each dose level and intensity of infection.

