## **17.2 Randomization**

Subjects will be assigned a randomization number by the unblinded third party pharmacist. The unblinded third party pharmacist will be supplied with 12 randomization schedules - one for each of the 3 severity levels (mild, moderate, severe) within each of the 3 dose cohorts (2 mg, 4 mg, 8 mg) and 3 additional schedules for the most severe (> 20 mf/mg of skin) subjects. Each randomization schedule will have 16 unique randomization numbers. The randomization numbers will be assigned by the unblinded third party pharmacist at the time of preparing the study medication and will be recorded on to the case report forms. Treatment groups will be blocked in groups of 4 with a 3 to 1 ratio of moxidectin to ivermectin. When the first male subject is enrolled, the assigned treatment (randomization number) will be selected from the top of the randomization list that corresponds to the subject's assigned stratum. The treatment (randomization number) for the first female subject will be selected from the bottom of the randomization list that corresponds to the subject's assigned stratum. The second male subject will be assigned the next available treatment from the top of the randomization list that corresponds to the subject's assigned stratum. The second female subject will be assigned the next available treatment from the bottom of the randomization list that corresponds to the subject's assigned stratum. Assignment to treatment group will continue in this manner until the entire cohort has been assigned to a treatment group. A new randomization schedule should be used when a new cohort is started.

At the end of the study, the randomization numbers will be used to identify the treatment group assigned to the subject.

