The clinical laboratory changes involve the peripheral blood leucocytes, aspartate aminotransferase (AST/SGOT) and alanine aminotransferase (ALT/SGPT) and sometimes lactate dehydrogenase (LDH) and gamma-glutamyl-transferase (GGT); microfilariae also appear in blood, urine, and other body fluids. The eosinophils exhibit the most prominent changes. There may be an initial eosinopenia followed several days later by a marked increase above pretreatment levels. A complete disappearance of eosinophils from the peripheral blood is the laboratory hallmark of a severe reaction. Lymphocyte counts may fall initially, followed by lymphocytosis, but not to the same extent as with eosinophils. Leucocytosis with neutrophilia is less common. Elevations in liver enzymes occur, but rarely exceed grade 2 and usually normalize by day 30. Levels of bilirubin and alkaline phosphatase are usually unchanged. Any deviation from this pattern of liver function abnormalities should prompt investigations for an intrinsic drug effect or a coincidental illness. Proteinuria may occur. Although the laboratory changes per se have little clinical significance, they give indirect evidence of the death of microfilariae and may even indicate the speed and severity of the reaction to the event.

The factors that govern the Mazzotti reaction include the intensity of infection, the dose regimen, and the microfilaricide used. These determine the onset, evolution, reaction severity, extent of the laboratory changes, and whether the reaction is mono- or biphasic. A notable exception occurs in subjects with hyper-reactive onchodermatitis (Sowda), where severe, predominantly cutaneous adverse effects occur even with very low skin microfilarial counts.

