## **21. STATISTICAL ANALYSIS**

### **21.1 Statistical Methods**

This is a randomized, double-blind, active-control, dose-escalation trial comparing 3 doses of moxidectin (2, 4, and 8 mg) with ivermectin, stratified by microfilariae density (mild, moderate, severe) and gender. Subjects will be treated as in subjects for the first 18 days and as outpatients for the remainder of the 18 month study.

The primary analysis population for safety will be the modified intent-to-treat (mITT) population, which consists of all subjects who receive study medication. For efficacy, the primary analysis population will be the evaluable subject population, which is defined as all subjects who receive study medication and have baseline and 18-month microfilariae count data. An mITT sensitivity analysis will also be performed to evaluate the effect on the efficacy results of dropouts occurring before 18 months.

The primary objective of the study is to evaluate the safety of escalating moxidectin regimens. Both the incidence of clinical AEs and clinically significant laboratory test results will be used to assess safety.

The primary efficacy endpoint is the reduction from baseline in skin microfilariae at 18 months. Microfilariae count will be defined as the geometric mean of skin microfilariae/mg taken at 4 sites (iliac crests and calves).

In addition, important secondary endpoints are the reduction from baseline in skin microfilariae load at day 8, 1 month, 2 months, 3 months, 6 months and 12 months, area under the curve (calculated by using the trapezoidal method through the 18 month visit), ocular examination (time of maximum reduction of microfilariae and number (%) of subjects with complete clearance) and nodulectomy (viability and fertility of macrofilariae) at 18 months.

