## **21.2 Methodology**

Initially, an overall among-group test will be performed to determine if any significant differences exist among the 4 treatment groups (2 mg, 4 mg, 8 mg moxidectin, and ivermectin). For this analysis the ivermectin control will be pooled over all nine cohorts (three dose groups). Following a significant overall result, paired comparisons (i.e., each moxidectin group versus ivermectin) will be performed to characterize the results. Prior to pooling the nine cohorts the ivermectin response for the nine cohorts will be graphically evaluated to ensure that there is no time effect on the pooled ivermectin results. For safety, moxidectin will be compared with ivermectin with respect to the incidence of AEs by using the Fisher's exact test. Laboratory data will be analyzed by using the analysis of covariance, adjusting for baseline. For efficacy, the microfilariae counts will be logarithmically transformed (Mosteller and Tukey) and analyzed by using the analysis of covariance, adjusting for baseline counts and the number of sites from which the microfilariae were taken. The latter covariate will be used to adjust for subjects who have fewer than 4 microfilarial collection sites. Factors in the model will include treatment group, covariates, level of microfilariae density (mild, moderate, severe), and gender. Also, a sensitivity analysis will be performed to examine the effect on results of second-order interactions. Data results will be summarized as adjusted geometric means. If the assumptions of normality or log-normality are not met, the data will be analyzed by using the Friedman Test, blocking on baseline skin microfilariae density and gender. In order to evaluate the robustness of the results, the microfilariae data will also be analyzed as a percent change from baseline. The proportion of subjects cured (i.e. with undetectable microfilariae) will also be evaluated.

For the analysis of microfilariae viability and fertility endpoints, proportions will be analyzed by using the Cochran-Mantel-Haenszel procedure blocking on baseline skin microfilariae density. If the overall test is significant, paired comparisons will be made comparing each moxidectin group with ivermectin.

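### The laboratory ANCOVA names baseline as its only adjustment, though allocation is stratified by density and gender; adding both strata is a nearly free gain in precision

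*Supplement*

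**What the plan says.** Section 21.2 (Methodology) of the latest protocol version gives the laboratory analysis one sentence: "Laboratory data will be analyzed by using the analysis of covariance, adjusting for baseline". No other term is named.

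The efficacy ANCOVA comes next in the same paragraph, and its description includes: "Factors in the model will include treatment group, covariates, level of microfilariae density (mild, moderate, severe), and gender".

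Section 21.1 describes the trial as "stratified by microfilariae density (mild, moderate, severe) and gender". Section 17.2 carries this out with 12 lists of 16 numbers: "one for each of the 3 severity levels (mild, moderate, severe) within each of the 3 dose cohorts", plus three further lists for the severe subjects. Within each list, "Treatment groups will be blocked in groups of 4 with a 3 to 1 ratio of moxidectin to ivermectin". Men are taken from the top of the list, while "The treatment (randomization number) for the first female subject will be selected from the bottom of the randomization list". Section 12.3 adds: "The study will aim to enroll equal numbers of men and women at each dose level and intensity of infection".

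Section 18.1 counts intensity of infection among the factors that govern the Mazzotti reaction and says of those factors: "These determine the onset, evolution, reaction severity, extent of the laboratory changes".

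**The concern.** A factor that is balanced between arms by design and also predicts the outcome belongs in the model. If it is left out, the treatment estimate is no less precise in truth, because balance has already removed the factor's contribution. The model does not know this. It leaves the factor's variance in the error term, so it reports too large a standard error and a nominal 5% test rejects less often than 5%.

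Density is the factor that matters here. The protocol itself links it to laboratory change. The pre-treatment value need not carry the same information, since the change follows the killing of microfilariae after dosing. The efficacy ANCOVA, its Friedman fallback, the viability and fertility tests and both ocular tests all adjust for or block on density. The laboratory ANCOVA could do so and, as written, does not.

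The laboratory comparison bears on the primary safety objective. In a safety comparison, a conservative test errs towards finding no difference.

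**Working it through.** **Inputs from the documents.** Group sizes are 48 per moxidectin dose and 48 pooled ivermectin (section 21.3), each made up of 12 mild, 12 moderate and 24 severe subjects by design. Tests are two-sided at 0.05 (section 21.2). With 8 men and 8 women on a list, each sex uses two whole blocks of 4, so the ratio is 6:2 within each sex and gender is balanced too.

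**The plan's own figures.** The plan gives no SD, effect size or power for any laboratory test, so there is none to reproduce. The only safety figures in section 21.3 are the chances of seeing at least one AE of grade 2 or higher, 1 − (1 − p)^n. They reproduce as 0.1136 and 0.7176 for n = 12, and 0.2143 and 0.9202 for n = 24, against the stated 0.114, 0.718, 0.214 and 0.92. They do not bear on the ANCOVA.

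**Assumed input.** Let r be the share of residual variance, after baseline, that density explains. The documents give no value, so a range is shown.

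**Formulas for a balanced design.**
- SE ratio, baseline-only to stratified: k = 1/√(1 − r)
- Actual two-sided alpha of the baseline-only test: 2 × [1 − Φ(1.96 k)]
- Its power where the stratified model has 80%: Φ(1.96 + 0.84 − 1.96 k)

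Example at r = 0.20: k = 1/√0.80 = 1.118 and 1.96 k = 2.19. Alpha is 2 × [1 − Φ(2.19)] = 0.028. Power is Φ(2.80 − 2.19) = Φ(0.61) = 0.729.

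| r (assumed) | SE ratio | Actual alpha | Power, baseline only | Power, stratified |
|---|---|---|---|---|
| 0 | 1.00 | 5.0% | 80% | 80% |
| 0.05 | 1.03 | 4.4% | 78.5% | 80% |
| 0.10 | 1.05 | 3.9% | 76.9% | 80% |
| 0.20 | 1.12 | 2.8% | 72.9% | 80% |
| 0.30 | 1.20 | 1.9% | 67.7% | 80% |

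**Check by simulation.** The protocol's allocation was simulated: 12 lists of 16, blocks of 4 at 3:1, men from the top and women from the bottom, 2,000 runs per setting. Neither model showed bias.

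| r (assumed) | SE ratio | Type I error, baseline only | Power, baseline only | Power, stratified |
|---|---|---|---|---|
| 0 | 1.00 | 4.7% | 78.0% | 77.8% |
| 0.05 | 1.03 | 4.5% | 79.4% | 80.2% |
| 0.10 | 1.055 | 4.0% | 77.0% | 79.5% |
| 0.20 | 1.12 | 3.1% | 73.5% | 80.5% |
| 0.30 | 1.20 | 2.2% | 66.4% | 79.3% |

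The mechanism shows directly at r = 0.20 under no effect. The estimate truly varied with SD 0.162 under both models, but the baseline-only model reported a mean SE of 0.183, against 0.1635 with the strata in.

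**Gender.** Assume a persistent difference between the sexes of 0.5 to 1.4 SD and a baseline-to-follow-up correlation of 0.6 to 0.9. Baseline then absorbs most of the difference, leaving r at 0.003 to 0.076 and an SE ratio of 1.002 to 1.04.

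**If cohorts do not all complete.** Section 10.1 allows progression to be held between cohorts, and section 21.2 pools ivermectin over all of them. A stop between dose levels keeps the 1:1:2 mix in every group. A stop within a level does not. If enrolment ended after cohort 7, the 8 mg arm would be 12 mild subjects. Pooled ivermectin would hold 3 × 4 = 12 mild, 2 × 4 = 8 moderate and 2 × 8 = 16 severe. Without density in the model, that contrast could be confounded by density as well as inefficient.

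**The case against.** The strongest reply is that the sentence is not a full model. It does not name treatment group either, and in the efficacy text the phrase about adjusting covers only covariates, with the factors listed later. On that reading the laboratory sentence is silent on density rather than excluding it, and a fuller model could sit in an analysis plan not shown. This has some force, but the protocol does state a model, and the factor list follows the efficacy ANCOVA. The same short edit settles either reading.

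Several limits on the point stand in full:
- The documents give no variance share. If density explains nothing beyond baseline, nothing is lost.
- Section 18.1 says liver-enzyme rises usually normalize by day 30, that bilirubin and alkaline phosphatase are usually unchanged, and that the laboratory changes in themselves have little clinical significance. Sodium, chloride, glucose and urea (section 15.3.5) are not tied to infection intensity. Any loss therefore falls on a subset of analytes, mainly at early visits.
- Gender contributes little.

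A reader might infer that the laboratory standard errors are certainly too large and that real effects will be missed, or that the safety decisions are undermined. The documents do not support this. The size of the loss is unknown. The primary objective is measured by AE incidence and clinically significant laboratory results, not by mean differences. Abnormal laboratory observations can also enter as graded AEs, and dose progression rests on expert review of graded events (section 18.2), not on this test.

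**Conclusion.** The point holds as a low-cost improvement in efficiency, not as a fault in validity. With all cohorts complete, the planned comparison is unbiased and errs on the conservative side. At an assumed density share of 5 to 20% of residual variance, the standard error is 3 to 12% too large and about 1.5 to 7 power points are lost from 80%. The loss reaches about 12 points only at 30%. These figures assume balanced arms and a density effect that is the same in both arms, and they describe a single pairwise contrast. The overall four-group test, which comes first, would be conservative for the same reason. Density carries the argument. Gender is worth including mainly to match the randomization and the efficacy model. Protection against density imbalance, should enrolment stop part-way through a dose level, is a second reason to include density.

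**What to change.** In section 21.2, replace the laboratory sentence with one that specifies an ANCOVA containing treatment group, the baseline value of the analyte, density level as a three-category factor, and gender. These are the factors the efficacy ANCOVA already uses.

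The cost is three degrees of freedom (two for density, one for gender). In a 48 versus 48 comparison, residual degrees of freedom fall from 93 to 90. Both variables are already collected. If density proves not to be prognostic, the simulation shows no loss from including it (SE ratio 1.00).

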| Efficacy Evaluation  | 
Efficacy evaluations (skin snips) will be performed at day 8, 1 month (<math>\pm 1</math> week), 2 months (<math>\pm 1</math> week), 3 months (<math>\pm 1</math> week), 6 months (<math>\pm 1</math> month), 12 months (<math>\pm 1</math> month) and 18 months (<math>\pm 1</math> month) after dosing and the number of microfilariae/mg of skin determined. Evaluation of the viability and fertility of the adult worms will occur at 18 months. All located nodules will be excised at 18 months, processed for histopathology, and slides interpreted by one or more observers. Microfilarial migration into blood and urine will be used as indirect evidence of the speed of microfilaricidal activity.
 
All subjects who have skin microfilariae at the 18-month visit will be treated with the approved dosage of ivermectin.
                                                                                                                                                                                                                                                            |
| Pharmacokinetics     | 
Blood samples for determination of moxidectin plasma concentrations will be collected within 2 hours prior to dosing (0 hr), and at 1, 2, 4, 8, 24, and 72 hours after study drug administration and on study days 8, 13, 18, 1 month (<math>\pm 1</math> week), 2 months (<math>\pm 1</math> week), 3 months (<math>\pm 1</math> week), 6 months (<math>\pm 1</math> month), and 12 months (<math>\pm 1</math> month). Pharmacokinetic (PK) samples will be drawn from all subjects in all cohorts with the exception of the 2nd group of 16 subjects with <math>>20</math> microfilariae/mg of skin in cohorts 3, 6, and 9. Samples from subjects will be analyzed by a validated bioanalytical method.
 
A PK analysis will be performed using model independent methods to characterize the PK parameters of moxidectin, such as maximum plasma concentration (<math>C_{max}</math>), time to reach the maximum plasma concentration (<math>t_{max}</math>), area under the plasma concentration vs. time curve (AUC) and the apparent terminal elimination half-life (<math>t_{1/2}</math>).
 |

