### 11.2 Secondary

The secondary objectives of this study are:

1. To determine doses that effectively eliminate microfilariae and prevent their reaccumulation in the skin as measured by the skin microfilarial loads at day 8, 1 month, 2 months, 3 months, 6 months, 12 months and 18 months after treatment.
2. To determine the viability and fertility of adult worms at 18 months.
3. To assess the pharmacokinetics of moxidectin in adult male and female subjects.

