#### **19.1.2 Secondary**

Secondary efficacy variables will include:

- The mean reduction from baseline, as well as the percentage of subjects with undetectable microfilariae, will be calculated by dose and severity of infection for each post treatment evaluation time point.
- The change from baseline in the mean number of skin microfilariae per milligram of skin sampled at 4 body locations (right and left iliac crests, right and left calves) at 12 months after test article administration.

- The change from baseline in the mean number of skin microfilariae per milligram of skin sampled at day 8, 1 month, 2 months, 3 months, and 6 months.
- The change from trough values to 12 months and 18 months post treatment in the mean number of skin microfilariae per milligram of skin sampled at 4 body locations (right and left iliac crests, right and left calves) to quantify the effect on the reproductive capacity of adult worms.
- The area under the curve (calculated by using the trapezoidal method through the 18 month visit)
- Ocular examination (time of maximum reduction of microfilariae and number (%) of subjects with complete clearance). The change from baseline in the mean number of ocular microfilariae measured in the anterior chamber. Living and dead microfilariae in the cornea and punctate opacities will also be counted. Retinal changes secondary to the disease will also be examined. Ocular examinations will be performed at baseline and on days 3 or 4, 7 or 8, 14 or 15, and at 1 month, 3 months, 6 months, 12 months and 18 months.
- Evidence of an effect on the viability and/or fertility of the macrofilaria will be obtained from the histologic examination of nodules excised at 18 months. Parameters to be evaluated include:
  - a. Viability (number live, moribund, dead)
  - b. Calcification (presence/absence)
  - c. Reproductive status:
    - i. Females:
      - Proportion:
        - 1. Number producing embryos up to the microfilarial stage
        - 2. Degenerated microfilariae in uterus
        - 3. Relict embryos
    - ii. Males:
      - Proportion with:
        - 1. Spermatogenesis normal or abnormal
    - iii. Other criteria:
      - Proportion of nodules with:
        - 1. Microfilariae in the capsule
        - 2. No male worms

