For ocular microfilariae, time to maximum reduction will be analyzed by using the Friedman Test blocking on baseline skin microfilariae density. The proportion of subjects with complete clearance will be analyzed by the Cochran-Mantel-Haenszel procedure blocking on baseline skin microfilariae density. If the overall test is significant, paired comparisons will be made comparing each moxidectin group with ivermectin.

All tests will be performed as 2-sided tests with  $\alpha = 0.05$ .

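### Adult-worm viability and fertility are defined per worm and per nodule but tested by CMH with no subject term; the unit of analysis is not named, and the 5% level is lost if worms or nodules are the rows

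*Supplement*

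**What the plan says.** References are to the later protocol version in the Supplement.

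- Section 11.2 lists as a secondary objective "To determine the viability and fertility of adult worms at 18 months".
- The synopsis (Efficacy Evaluation) sets the sampling: "All located nodules will be excised at 18 months, processed for histopathology".
- Section 19.1.2 defines the variables at two levels below the subject. Worms are counted, as in "Viability (number live, moribund, dead"; female and male worms are classified by reproductive status. Nodules are a second denominator, under "Proportion of nodules with". One nodule criterion is the absence of male worms, so a nodule may hold more than one worm.
- Section 21.2 names the test: "For the analysis of microfilariae viability and fertility endpoints, proportions will be analyzed by using the Cochran-Mantel-Haenszel procedure blocking on baseline skin microfilariae density". The sentence says microfilariae, but sections 11.2 and 21.1 show that adult worms are meant. Paired comparisons of each dose with ivermectin follow a significant overall result.
- Section 21.2 also says "All tests will be performed as 2-sided tests with" alpha 0.05.
- Section 17.2 assigns treatment to subjects, not to worms or nodules.

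No text for these endpoints names the unit of analysis, a subject term, a cluster adjustment or a per-subject summary.

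**The concern.** An ordinary CMH test on a table of worms or nodules treats each row as an independent observation. Worms from one subject share a dose, a drug exposure and an infection history, so their outcomes are likely to be alike. The synopsis itself plans to correlate pharmacokinetic parameters, gender and severity with efficacy, so it expects response to vary between subjects. If that correlation is ignored, the variance is understated and the test rejects too often.

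The text leans towards worm or nodule rows. Where section 21.2 means subjects it says so, both for undetectable skin microfilariae and for ocular clearance. For viability and fertility it speaks only of proportions, and section 19.1.2 supplies worms and nodules as the denominators.

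The introduction argues that a drug acting on adult worms is needed and that moxidectin may be one. A false positive here would support exactly that claim. An unnamed unit also leaves a valid and an invalid analysis both open after unblinding.

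**Working it through.** **Inputs from the documents**

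- Two-sided alpha of 0.05 (section 21.2).
- Four groups in the overall test (3 df), then each dose against ivermectin (1 df) (section 21.2).
- 48 subjects per group (section 21.3). By density stratum, each moxidectin dose has 16 × 3/4 = 12 mild, 12 moderate and 32 × 3/4 = 24 severe. Pooled ivermectin has 3 × 4 = 12, 3 × 4 = 12 and 3 × 8 = 24.

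**Inputs not in the documents (assumed)**

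- Worms or nodules per subject, m: 2 to 5 in the results below.
- ICC within subject: 0.05 to 0.3.
- Null rate of 0.4 in the simulation.

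**Step 1: the plan's own level.** The CMH test was simulated with independent worms (ICC 0, m = 4, 3,000 runs). It rejected in 4.7% of runs overall and 5.2% pairwise. The Monte Carlo standard error is √(0.05 × 0.95/3000) = 0.4 percentage points, so the stated 5% is reproduced when there is no clustering.

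**Step 2: approximation with clustering.** The design effect is DE = 1 + (m − 1) × ICC. The actual error is 2[1 − Φ(1.96/√DE)] for a pairwise test and P(χ²₃ > 7.815/DE) for the overall test.

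Example with m = 3 and ICC 0.1: DE = 1 + 2 × 0.1 = 1.2. Then 1.96/√1.2 = 1.789 gives 7.4% pairwise, and 7.815/1.2 = 6.51 gives 8.9% overall.

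| m | ICC | DE | Pairwise | Overall |
|---|---|---|---|---|
| 2 | 0.05 | 1.05 | 5.6% | 5.9% |
| 2 | 0.1 | 1.1 | 6.2% | 6.9% |
| 3 | 0.1 | 1.2 | 7.4% | 8.9% |
| 3 | 0.2 | 1.4 | 9.8% | 13.4% |
| 4 | 0.1 | 1.3 | 8.6% | 11.1% |
| 4 | 0.2 | 1.6 | 12.1% | 18.0% |
| 5 | 0.3 | 2.2 | 18.6% | 31.4% |

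**Step 3: simulation check.** Beta-binomial outcomes with the 12/12/24 strata, 3,000 runs per setting. The first two error columns put worms in the rows. The last takes one proportion per subject and applies a stratified mean-score CMH (overall test).

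| Setting | Pairwise, worm rows | Overall, worm rows | Overall, subject level |
|---|---|---|---|
| m = 2, ICC 0.1 | 6.3% | 6.5% | 4.7% |
| m = 3, ICC 0.1 | 7.9% | 9.3% | 4.9% |
| m = 4, ICC 0.2 | 11.0% | 16.7% | 4.5% |
| m = 5, ICC 0.3 | 18.5% | 30.0% | 5.1% |
| m varying, mean 4, ICC 0.2 | 17.6% | 30.2% | 5.2% |
| m varying, mean 5, ICC 0.3 | 26.7% | 49.0% | 4.3% |

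The simulation agrees with the approximation for equal counts. Unequal counts make the inflation worse. Across all ten settings run, the subject-level test stayed between 4.3% and 5.3%.

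**Step 4: the gate.** The pairwise figures are for stand-alone tests, so they are upper limits for a single comparison made only after a significant overall test. The gate does not restore 5%, because the overall test is itself inflated, and by more.

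**The case against.** The strongest reply is that the plan never says worms or nodules are the rows. The efficacy population is made up of subjects, the sample size counts subjects, and the parallel CMH analysis of ocular clearance is per subject. A mean-score CMH on one fraction per subject is itself a CMH procedure and keeps about 5%. This stands in part. A reader might infer that the protocol declares worms independent, or that CMH as such is wrong here; the text supports neither. But the definitions in section 19.1.2 point to worm and nodule denominators, and nothing in section 21.2 steers the analyst to a subject-level summary.

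A second reply is that no separate analysis plan is shown, and that reducing histology data to an analysis variable is often left to one. That would excuse missing detail. It does not cure a test that the protocol itself names and that, applied to the denominators the protocol itself gives, understates the variance.

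A third reply is that the size of the inflation rests entirely on assumed worm counts and ICCs. This stands. Section 12 calls the area largely hypoendemic, and a quarter of subjects (3 × 16 of 192) enter with fewer than 10 microfilariae per mg, so small counts are possible. Male-worm and nodule endpoints will also have different cluster sizes from the others.

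**Conclusion.** The point holds as a fault of specification with a real consequence: the unit is unnamed, there is no provision for clustering, and the natural reading of the endpoint definitions loses the 5% level. With worm or nodule rows and equal counts per subject, the pairwise error is about 6% for 2 per subject with ICC 0.05 to 0.1, and 7 to 12% for 3 to 4 per subject with ICC 0.1 to 0.2. It is 19% or more for 5 per subject with ICC 0.3. The corresponding overall errors are about 6 to 7%, 9 to 18% and 31%. All of these rest on assumed m and ICC.

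A reader might take an error of 8 to 30% or more as an established property of the plan. The documents do not support that, since they contain neither input and the mild cases lie near 6%. Nor is the trial's main conclusion at risk. The primary objective is safety and the primary efficacy variable is skin microfilariae, both measured per subject. The fault is confined to one secondary objective. It should be corrected, preferably before unblinding.

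**What to change.** Amend section 21.2 as follows.

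1. Name the subject as the independent unit for all worm and nodule endpoints.
2. Choose one analysis in advance. Either compute one proportion per subject and use a stratified mean-score CMH or stratified Wilcoxon test, or fit a logistic GEE or mixed model clustered on subject, with treatment and density stratum as terms.
3. State that subjects without nodules do not contribute to these endpoints, and report their number by group.
4. Keep the ordinary CMH for outcomes with one value per subject, such as ocular clearance.

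The cost is wording only, with no extra data. Intervals will be wider than those from a worm-level table. With one proportion per subject, a subject with few worms counts as much as one with many.

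### The adult-worm viability and fertility CMH tests block on skin density but not on gender, a declared allocation stratum; this costs power only if gender is clearly prognostic

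*Supplement*

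**What the plan says.** All references are to the amended protocol, the later version in the Supplement.

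- Section 21.1 calls the trial "stratified by microfilariae density (mild, moderate, severe) and gender".
- Section 17.2 supplies twelve lists of 16 numbers in blocks of four at 3:1. Men are taken from the top of the list, and for women: "The second female subject will be assigned the next available treatment from the bottom of the randomization list". Section 12.3 adds: "The study will aim to enroll equal numbers of men and women at each dose level and intensity of infection".
- Section 21.2 puts "level of microfilariae density (mild, moderate, severe), and gender" into the skin-count ANCOVA. If normality fails, the fallback is a "Friedman Test, blocking on baseline skin microfilariae density and gender".
- For viability and fertility the same section names the "Cochran-Mantel-Haenszel procedure blocking on baseline skin microfilariae density", followed by paired comparisons with ivermectin. The sentence says microfilariae, but the endpoints of that name in sections 19.1.2 and 21.1 belong to the adult worms. The ocular tests also block on density alone.
- Section 19.1.2 defines the histology endpoints partly as worm counts, "Viability (number live, moribund, dead"), and partly as "Proportion of nodules with" given features.

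**The concern.** Adult-worm viability and fertility at 18 months is the second secondary objective (section 11.2). When allocation balances a factor and the analysis ignores it, the variation due to that factor stays in the test's variance although it cannot contribute to the treatment difference. If the factor is prognostic, the test rejects too rarely and loses power. The plan is also inconsistent: gender is adjusted for on the skin-count endpoint and dropped, without explanation, on the worm endpoint.

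**Working it through.** **Does allocation balance gender?** With 8 men and 8 women on a list of 16, the men use two whole blocks of four and the women the other two. Each gender then splits exactly 6:2. Pooling ivermectin over the three dose groups gives 3 × 2 = 6 men and 6 women in the mild stratum, the same in the moderate, and 12 and 12 in the severe. Each moxidectin dose has the same numbers, 48 per arm in all. With 7 men on a list, 5 or 6 receive moxidectin, so balance is near but not exact.

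**Why size falls.** Assume a control rate centred on 50%, with rates p and 1 − p in the two genders. The density-only test uses a variance proportional to 0.5 × 0.5 = 0.25. With gender balanced, the true variance is proportional to p(1 − p). The ratio is r = p(1 − p)/0.25, and the approximate size is 2[1 − Φ(1.96/√r)].

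- Odds ratio 2 (p = 0.586): r = 0.971, size 0.047
- Odds ratio 4 (p = 0.667): r = 0.889, size 0.038
- Odds ratio 5.4 (p = 0.70): r = 0.84, size 0.033

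**Simulation, one outcome per subject.** 48 v 48, density strata 12/12/24 per arm, half men, two-sided 5%. The plan states no power for these tests, so there is no figure of its own to reproduce. The control rate, treatment effect and gender effects are assumptions. The treatment odds ratio is 3.4, except in the 5.4 row, where it is exp(1.2) = 3.3.

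| Gender OR | Size, density only | Size, density and gender | Power, density only | Power, density and gender |
|---|---|---|---|---|
| 1 | 0.052 | 0.052 | 80.0% | 80.0% |
| 1.5 | 0.051 | 0.051 | 79.7% | 80.0% |
| 2 | 0.051 | 0.052 | 78.4% | 79.2% |
| 4 | 0.039 | 0.049 | 73.1% | 77.1% |
| 5.4 (70% v 30%) | 0.035 | 0.050 | 67.7% | 73.7% |

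Repeat runs of the 5.4 case gave a size of 0.032 to 0.033 and power of 67.5% v 73.7 to 73.8%. The gain is 0.8 points at 2, 4.0 at 4 and about 6 at 5.4.

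**Fewer evaluable subjects.** The fractions are assumptions. Power is density only v density and gender, at log odds ratio 1.2.

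- No gender effect: 63.1% v 62.5% with 70% evaluable, 47.8% v 46.3% with 50%, 39.6% v 37.4% with 40%, 25.2% v 22.6% with 25%.
- 60% v 40% by gender: 37.3% v 36.5% with 40% evaluable.
- 70% v 30% by gender: 51.1% v 56.8% with 70% evaluable, 37.8% v 41.4% with 50%, 30.4% v 33.2% with 40%.

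With 70% or 50% evaluable, the size with six blocks stayed at 0.048 to 0.051.

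**Worms as units.** If each worm enters the density-blocked test as if independent, the size under a true null is 0.075 for 3 worms per subject and intraclass correlation 0.1, 0.139 for 5 and 0.2, and 0.324 for 8 and 0.4. Worms per subject and the correlation are assumptions. This error runs the other way, and a gender block does not remove it.

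**The case against.** A reader might infer that the planned tests are conservative and lose power as they stand. The documents do not support that. Nothing in them says that gender predicts worm viability or fertility, and up to an odds ratio of about 2 the effect is negligible.

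The direction itself depends on the unit of analysis. Section 19.1.2 counts worms and nodules, the synopsis has all located nodules excised, and section 21.2 names no subject-level summary. If worms or nodules are the units, the test may be anti-conservative. This stands, and it is why the fix must name the unit.

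Nor is the gender block free. Four of the six blocks hold 6 v 6 subjects before attrition. Some subjects may have no usable nodule, and section 15.2 does not collect nodulectomy results from early terminators on the CRF. Coarser blocking is then a defensible choice when gender is not prognostic. The measured cost is small, 0.6 to 2.6 points over the evaluable fractions tried, and at 70% v 30% by gender six blocks still gain 2.8 to 5.7 points.

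The ocular extension is weaker. Sections 10.1 and 12.2 bar ocular involvement in the mild cohorts, so that stratum has nothing to clear, and the other strata may be sparse. With moderate and severe strata only, 40% evaluable, log odds ratio 1.6 and no gender effect, the added block lowered power from 46.0% to 44.0%.

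**Conclusion.** The omission is real and unexplained: gender is declared, built into allocation and used for skin counts, but not for the worm proportions. Its consequence is conditional. For subject-level proportions it costs under about 1 point of power up to a gender odds ratio of 2, about 4 points at 4 and about 6 at 5.4, with size near 0.033 to 0.039 in the last two cases. These figures rest on complete data, equal numbers of men and women, and an assumed 50% control rate and treatment effect. It would go too far to say that the planned test is conservative, that adding gender costs nothing, or that it cures the handling of several worms per subject. This is a minor point on a secondary endpoint. The unit of analysis is the larger gap in the same sentence of the plan.

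**What to change.** In section 21.2, for the worm viability and fertility proportions, add the words 'and gender' after the density blocking factor, giving six blocks and matching the Friedman fallback. In the same sentence, state that the proportions are analysed as one summary per subject, or by a cluster-adjusted method such as a clustered CMH test, GEE or a mixed model. Adding gender to the ocular clearance proportion is optional and for consistency only. Settle the wording before unblinding, so that blocking factors are not chosen with results in view.

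The cost is a short text change using data already collected, plus about 1 to 2 points of power if gender proves not prognostic and many subjects lack evaluable nodules.
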